#### Assessments

3.2.4

##### Data collection time points

3.2.4.1

Assessments will take place at screening (T0), baseline (T1), 10 days post-randomization (T2, only IG), and 4 weeks post-randomization (T3, post-intervention). Data collection includes online self-reports and telephone-based diagnostics (SCID-5). In-app assessments include daily EMA (PHQ-4) and repeated measures every 4 days (PHQ-4, TYDQ, CBTSQ [Things You Do Questionnaire and Cognitive-behavioral Therapy Skills Questionnaire]). In the IG, additional qualitative interviews after the app usage phase take place to explore their experiences with the study process, app usage, its acceptance, as well as facilitators and barriers to its application. Those who have discontinued the intervention will also be invited to identify barriers and reasons for dropout. An overview of all assessments and instruments is provided in Table 2.

**Table 2 tab2:** Assessment overview.

Instrument	Variable	Time of measurement					
		Screening	T0 Baseline	T1 10 Days	T2 Post	Daily	Course 4-days
Self-developed items	Inclusion criteria	x					
PHQ-ADS	Anxiety and depression	x					
BDI-II Item 9	Suicidal thoughts and behaviors	x			x		
PHQ-4	Anxiety and depression		x		x	x	x
Self-developed items	Sociodemographic data		x				
Self-developed items	Current medication		x		x		
ZUF-8	Treatment satisfaction			x	x		
Self-developed items				x	x		
TYDQ	Behaviors that promote mental health		x		x		x
INEP-On	Positive and negative effects of app use				x		
CBTSQ	CBT-Skills		x		x		x
SUS	Usability			x	x		
Self-developed items	Acceptability of data collection procedures				x		
Self-developed items	Concurrent treatment				x		
Self-developed items	Reasons for drop-out			x	x		
Diagnostic interviews							
SCID-5	Mental disorders, comorbidities, severity and chronicity		x				

PHQ-ADS, Patient Health Questionnaire Anxiety and Depression Scale; PHQ-4, Patient Health Questionnaire-4; BDI-2, Beck Depression Inventory-2; ZUF-8, Questionnaire for Patient Satisfaction 8; TYDQ, Things You Do Questionnaire; INEP-On, Inventory for Assessment of Negative Effects of Psychotherapy adapted to Online interventions; CBTSQ, Cognitive-Behavioral Therapy Skills Questionnaire; SUS, System Usability Scale; SCID-5, Structured Clinical Interview for DSM-5.

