**Figure 1 fig1:**
[figure not shown]
Study design. T0, Screening; T1, Baseline; T2, 10 days post-randomization; T3, 4 weeks post-randomization; JITAI, Just-in-Time Adaptive Interventions; EMA, Ecological Momentary Assessment.

The trial was approved by the local Ethics Committee of the University of Marburg (CaYou2025-05v) and will be reported in accordance with the Consolidated Standards of Reporting Trials (CONSORT) 2025 Statement and its extensions for pragmatic trials and psychological intervention trials (66). Qualitative analyses will follow the Consolidated Criteria for Reporting Qualitative Studies (COREQ) checklist (56). The trial protocol was developed according to the updated SPIRIT guidelines (57) and is registered on the Open Science Framework: https://doi.org/10.17605/OSF.IO/EYXD2.

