1) Recruitment capability and resulting sample characteristics: Recruitment capability will be assessed by the number of individuals expressing interest in study participation, the intervention uptake rate, and the time required to reach the target sample. The traffic light system will evaluate whether the planned sample size (*N* = 60) is achieved within the 12-week recruitment period (see Table 3). Sample characteristics will be collected through sociodemographic data (e.g., age, gender, education, employment, relationship and parental status, residence size, nationality, ethnicity, migration status), family history of anxiety or depression, prior diagnoses, psychotherapy history, current medication or treatment, and experience with digital mental health tools.2) Data collection procedures and outcome measures: The appropriateness of data collection will be assessed through EMA and T2 data completeness, psychometric evaluation of outcome measures, and feedback from the study team. Participant perspectives on acceptability and appropriateness will be gathered at T2 using self-developed items and in the qualitative telephone interviews based on a custom interview guide (IG participants only).3) Acceptability and suitability of intervention and study procedures: Acceptability, satisfaction, and usability of the app will be measured using the German version (ZUF-8; *α* = 0.90, 8 items, score range: 8–32) of the Client Satisfaction Questionnaire (CSQ) (71), the System Usability Scale (SUS; *α* = 0.91, 10 items, score range: 0–40) (72), and self-developed items. At T2, qualitative telephone interviews will further explore participants’ experiences with the app’s features, content, and overall impressions. Intervention adherence will be measured via user engagement metrics (e.g., number of modules and exercises completed, usage days during the 4-week period, buddy interactions, and optional sensor data). Reasons for dropout will be assessed through self-developed items and within the qualitative interview at T2.4) Resources and ability to manage and implement the study and intervention: The study team will document time and personnel resources needed for app development, study administration, and participant support.5) Participant responses to the intervention: Symptoms of anxiety and depression will be measured using the Patient Health Questionnaire Anxiety and Depression Scale (PHQ-ADS; *α* = 0.88–0.92, 16 items; score range: 0–48) (73), which combines the Patient Health Questionnaire 9 (PHQ-9; *α* = 0.89, 9 items, score range: 0–27) (51, 74) and the Generalized Anxiety Disorder Scale 7 (GAD-7; *α* = 0.89, 7 items, score range: 0–21) (75). The PHQ-ADS has shown high internal consistency (*α* = 0.88–0.92). Cognitive behavioral skills will be measured using the Cognitive-behavioral Therapy Skills Questionnaire (CBTSQ; *α* = 0.90, 16 items, score range 16–80), covering behavioral activation (*α* = 0.85) and cognitive restructuring (*α* = 0.88) (76). The Things You Do Questionnaire (TYDQ; *α* = 0.90, 15 items, score range: 0–60) (77) will assess engagement in positive routines and meaningful activities, with higher scores indicating greater engagement (*α* = 0.90). Qualitative interviews at T2 will explore the perceived effects of the app from the IG participants’ perspective.6) Risks and negative events: The benefit–risk ratio will be assessed by tracking adverse events, including reliable symptom improvement and deterioration according to the reliable change index (RCI) by Jacobson and Truax for the PHQ-ADS, indicating a decrease or increase of >1.96 from T1 to T3 as well as suicidal thoughts and behaviors (78). These will be measured at T2 using the INEP-On (Inventory for Assessment of Negative Effects of Psychotherapy adapted to online interventions; *α* = 0.86, 21 items) (79), item 9 of the PHQ-ADS (73), and item 9 from the BDI-II (80). Qualitative interviews will further explore perceived negative effects of the app.

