##### Qualitative interviews

3.2.4.3

At T2, qualitative interviews with IG participants will explore experiences related to feasibility criteria (see Table 3), including user satisfaction, usability, and practical applicability in daily life. To ensure data saturation, at least 20 participants will be interviewed (53). Interviews will be conducted by trained staff, audio-recorded, and transcribed verbatim using a standardized guide.

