#### Safety concept

3.2.6

Data on adverse and serious adverse events will be collected at different assessment points throughout stage II as recommended (81). Suicidal thoughts and behaviors will be assessed with PHQ-ADS item 9 (73) and BDI-II item 9 (80) at screening, and INEP-On item 20 at T2. Other negative events will be assessed with the INEP-On at T2. Relevant indications may also emerge from participants’ responses during the screening or qualitative post-intervention interview.

A detailed safety protocol, based on existing recommendations (77) outlines procedures for managing negative events. These include automated provision of help resources via questionnaires and email, and individual therapeutic phone consultations following a structured emergency plan tailored to the severity of suicidal ideation. A licensed psychotherapist will be available for consultations, and screening interviewers will be trained and supervised in implementing the emergency plan. All adverse events will be documented.

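### Visit labels conflict, and the follow-up harms and suicidality assessment is specified in three different ways, so an input to feasibility criterion 7 is not fixed

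*Protocol article*

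**What the plan says.** **Visit labels.** The Figure 1 legend (section 3.2.1) gives "T0, Screening; T1, Baseline; T2, 10 days post-randomization; T3, 4 weeks post-randomization". The text of section 3.2.4.1 agrees and limits the day-10 visit to the intervention group: "10 days post-randomization (T2, only IG), and 4 weeks post-randomization (T3, post-intervention". Table 2, in the same section, has an unnumbered screening column, then T0 for baseline, then "T1 10 Days T2 Post". It has no T3.

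**Uses of T2.** Section 3.2.4.2, domain 2: "The appropriateness of data collection will be assessed through EMA and T2 data completeness". Section 3.2.4.3: "At T2, qualitative interviews with IG participants will explore experiences related to feasibility criteria". Section 3.2.4.2, domain 6, on adverse events and suicidality: "These will be measured at T2 using the INEP-On". The sentence just before that one sets the PHQ-ADS reliable change between T1 and T3.

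**Suicidality instruments.** Domain 6 adds to INEP-On "item 9 of the PHQ-ADS (73), and item 9 from the BDI-II (80", all at T2. Section 3.2.6 puts the PHQ-ADS and BDI-II items "at screening, and INEP-On item 20 at T2". Table 2 marks BDI-II item 9 at screening and post, INEP-On at post, and PHQ-ADS at screening only.

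**Decision rule.** Under section 3.2.5.1 the intervention counts as feasible only if every criterion in Table 3 is yellow or green. Row 7 (risk–benefit) is red for serious intervention-related events, with suicidal thoughts as the example, and for symptom deterioration.

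**The concern.** Two separate defects sit on top of each other.

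The first is a labelling clash. Anyone who builds the survey or writes the report from the text and Figure 1 will read T2 as day 10. Anyone who works from Table 2 will read it as post-intervention.

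The second does not go away once the labels are settled: three places name three different sets of follow-up suicidality instruments. The article does not say which set is collected, nor in which arm.

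At stake is a safety outcome that also drives a stated go/no-go criterion. If the survey is built to the wrong version, suicidality and deterioration data that row 7 relies on will not exist at follow-up, and they cannot be collected later.

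**Working it through.** No arithmetic applies. The check sets the statements side by side.

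**Step 1: visit labels**

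| Visit | Figure 1 legend and 3.2.4.1 text | Table 2 header |
|---|---|---|
| Screening | T0 | no number |
| Baseline | T1 | T0 |
| Day 10 | T2 (intervention group only, per 3.2.4.1) | T1 |
| Week 4, post | T3 | T2 |

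From baseline on, every label is shifted by one. T2 is day 10 in two places and post in a third.

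**Step 2: which meaning fits each use**

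- Reliable change from T1 to T3 (3.2.4.2, domain 6): only the Figure 1 numbering has a T3, so this means baseline to week 4.
- INEP-On and BDI-II item 9 at T2 (same domain, next sentence): Table 2 marks both at post and neither at day 10, so this fits only the Table 2 numbering.
- Interviews at T2 (3.2.4.2 and 3.2.4.3): 3.2.4.1 puts them after the period of app use, so T2 here means post.
- Data completeness at T2 (domain 2): Table 3 row 2 scores completeness at post-assessment, so T2 here means post.
- INEP-On at T2 (3.2.6): Table 2 again marks it at post only.

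Domain 6 therefore uses both numberings in consecutive sentences.

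**Step 3: follow-up suicidality, reading T2 as post throughout**

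| Instrument | 3.2.4.2, domain 6 | 3.2.6 | Table 2 |
|---|---|---|---|
| INEP-On | yes | yes (item 20) | yes |
| BDI-II item 9 | yes | screening only | yes |
| PHQ-ADS item 9 | yes | screening only | screening only |

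Only INEP-On is common to all three. Beyond it, the lists contain two, none and one further instrument.

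**Step 4: what each version leaves unobtainable**

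- *Table 2.* PHQ-ADS is collected at neither end of the baseline to week 4 interval. Even if the screening value stood in for baseline, there would be no week-4 value. The PHQ-ADS reliable change and the follow-up PHQ-ADS item 9, both required by domain 6, cannot be computed.
- *Section 3.2.6.* The only follow-up suicidality item is in INEP-On, which Table 2 describes as measuring what app use does to the user. Wait-list participants get access after 4 weeks (3.2.1), so at week 4 they have no app use to report on. No suicidality item independent of app use is listed at follow-up.
- *In-app measures.* The daily and 4-day instruments in Table 2 are PHQ-4, TYDQ and CBTSQ. None is listed as a suicidality measure, so they do not fill the gap.

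**Step 5: link to the decision.** Reliable deterioration and suicidal thoughts are the harms that domain 6 tracks, and row 7 names both deterioration and suicidal thoughts among its triggers for red. A red in any row means the feasibility condition in 3.2.5.1 is not met.

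**The case against.** The best defence is that the label clash can be resolved from the document itself. Table 2 places INEP-On and BDI-II item 9 at post and not at day 10. Table 3 row 2 fixes completeness at post-assessment. Sections 3.2.4.1 and 3.2.6 both put the interviews after the intervention. On that evidence, T2 in 3.2.4.2, 3.2.4.3 and 3.2.6 means post. This stands, and it makes the label part mainly editorial.

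It also disposes of a stronger reading. Someone who applies the 3.2.4.1 definition literally might infer that harms are assessed only on day 10 and only in the intervention group, with the rest of the four weeks uncovered, no control assessed, and completeness scored at a visit that controls do not attend. The documents do not support this. Besides the points above, 3.2.6 provides for adverse events to be collected at several points during stage II and for all of them to be documented. Only the day-10 visit is restricted to one arm; Table 2 puts no arm restriction on BDI-II item 9 at post.

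A reader might also infer that row 7 needs a control-arm event rate. It does not: the row is worded in terms of events related to the intervention, and the comparison with controls belongs to row 6. A between-arm test for row 7 would be a preference.

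The defence does not reach the instrument lists. They differ even when every T2 is read as post, and no passage says which one prevails.

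**Conclusion.** The point holds as an internal contradiction. There are two visit numberings, mixed within domain 6 of 3.2.4.2, and three incompatible specifications of follow-up suicidality. The labels can probably be resolved in favour of post-intervention; the instruments cannot be resolved from the document. The practical size is that, depending on which place is followed, either the PHQ-ADS reliable change and PHQ-ADS item 9 are missing at follow-up, or suicidality at follow-up rests on one item in an app-effects questionnaire that does not suit the wait-list arm. Both bear on row 7, where red blocks a feasible rating.

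This rests on reading Table 2 and the list in 3.2.6 as complete for the instruments they name. It does not rest on harms being measured at day 10, and no number of missed events or days is claimed. It should be settled before follow-up data are collected.

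**What to change.** 1. Use one visit numbering in the Figure 1 legend, 3.2.4.1, Table 2, 3.2.4.2, 3.2.4.3 and 3.2.6, and correct each T2 to the visit intended.
2. Reconcile 3.2.4.2, 3.2.6 and Table 2 into a single harms and suicidality schedule that states the instruments, the visit and the arm or arms assessed. Which schedule is right is for the sponsor to decide.
3. Either schedule PHQ-ADS at both visits that the reliable-change rule needs, or base that rule on an instrument already collected at both.
4. Check the survey build against the reconciled schedule.

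The cost is edits to text and one table, plus the build check. Adding PHQ-ADS would cost participants 16 items at each added visit; choosing an instrument already collected at baseline and post would add nothing.

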##### Feasibility measures

3.2.4.2

A traffic light system with predefined criteria (see Table 3) was developed to assess feasibility. Following Orsmond and Cohn, six domains will be evaluated: (1) recruitment capability and resulting sample characteristics, (2) data collection procedures and outcome measures, (3) acceptability and suitability of intervention and study procedures, (4) resources and ability to manage and implement the study and intervention, (5) participant responses to the intervention, and (6) risks and adverse events (70).

1) Recruitment capability and resulting sample characteristics: Recruitment capability will be assessed by the number of individuals expressing interest in study participation, the intervention uptake rate, and the time required to reach the target sample. The traffic light system will evaluate whether the planned sample size (*N* = 60) is achieved within the 12-week recruitment period (see Table 3). Sample characteristics will be collected through sociodemographic data (e.g., age, gender, education, employment, relationship and parental status, residence size, nationality, ethnicity, migration status), family history of anxiety or depression, prior diagnoses, psychotherapy history, current medication or treatment, and experience with digital mental health tools.2) Data collection procedures and outcome measures: The appropriateness of data collection will be assessed through EMA and T2 data completeness, psychometric evaluation of outcome measures, and feedback from the study team. Participant perspectives on acceptability and appropriateness will be gathered at T2 using self-developed items and in the qualitative telephone interviews based on a custom interview guide (IG participants only).3) Acceptability and suitability of intervention and study procedures: Acceptability, satisfaction, and usability of the app will be measured using the German version (ZUF-8; *α* = 0.90, 8 items, score range: 8–32) of the Client Satisfaction Questionnaire (CSQ) (71), the System Usability Scale (SUS; *α* = 0.91, 10 items, score range: 0–40) (72), and self-developed items. At T2, qualitative telephone interviews will further explore participants’ experiences with the app’s features, content, and overall impressions. Intervention adherence will be measured via user engagement metrics (e.g., number of modules and exercises completed, usage days during the 4-week period, buddy interactions, and optional sensor data). Reasons for dropout will be assessed through self-developed items and within the qualitative interview at T2.4) Resources and ability to manage and implement the study and intervention: The study team will document time and personnel resources needed for app development, study administration, and participant support.5) Participant responses to the intervention: Symptoms of anxiety and depression will be measured using the Patient Health Questionnaire Anxiety and Depression Scale (PHQ-ADS; *α* = 0.88–0.92, 16 items; score range: 0–48) (73), which combines the Patient Health Questionnaire 9 (PHQ-9; *α* = 0.89, 9 items, score range: 0–27) (51, 74) and the Generalized Anxiety Disorder Scale 7 (GAD-7; *α* = 0.89, 7 items, score range: 0–21) (75). The PHQ-ADS has shown high internal consistency (*α* = 0.88–0.92). Cognitive behavioral skills will be measured using the Cognitive-behavioral Therapy Skills Questionnaire (CBTSQ; *α* = 0.90, 16 items, score range 16–80), covering behavioral activation (*α* = 0.85) and cognitive restructuring (*α* = 0.88) (76). The Things You Do Questionnaire (TYDQ; *α* = 0.90, 15 items, score range: 0–60) (77) will assess engagement in positive routines and meaningful activities, with higher scores indicating greater engagement (*α* = 0.90). Qualitative interviews at T2 will explore the perceived effects of the app from the IG participants’ perspective.6) Risks and negative events: The benefit–risk ratio will be assessed by tracking adverse events, including reliable symptom improvement and deterioration according to the reliable change index (RCI) by Jacobson and Truax for the PHQ-ADS, indicating a decrease or increase of >1.96 from T1 to T3 as well as suicidal thoughts and behaviors (78). These will be measured at T2 using the INEP-On (Inventory for Assessment of Negative Effects of Psychotherapy adapted to online interventions; *α* = 0.86, 21 items) (79), item 9 of the PHQ-ADS (73), and item 9 from the BDI-II (80). Qualitative interviews will further explore perceived negative effects of the app.

**Table 3 tab3:** Traffic light system for assessing feasibility.

Traffic light system for assessing feasibility	Green	Yellow	Red
1. Participants recruited during the planned period (%)	*N* = 60 (100%)	*N* = 45–59 (75–98%)	*N* < 45 (<75%)
2. Participants with complete data at post-assessment (percentage of the total sample)	>70%	50–70%	<50%
3. Completed EMA data (at least one EMA completed per day; percentage of the total sample)	>60%	40–60%	<40%
4. Omega value for two-thirds of the outcome questionnaires	≥0.70	0.60–0.69	<0.59
5. Satisfaction (ZUF-8)	*M* > 26	*M* = 24–26	*M* < 24
6. Pre-post change in the PHQ-4 scores compared to the control group (depression and anxiety subscales)	Baseline score ≤3: No reliable deterioration, indeterminate, or reliable improvement Baseline score > 3: No deterioration or improvement reliable to deterioration and improvement	No improvement reliable to improvement in participants with a baseline score > 3	Symptom deterioration reliable to deterioration
7. Risk–benefit ratio	Positive	Negative: Isolated negative intervention-related events, that can be addressed by revising the intervention or study	Negative: Serious adverse intervention-related events (e.g., suicidal thoughts), symptom deterioration

EMA, Ecological Momentary Assessment; ZUF-8, Questionnaire for Patient Satisfaction 8.

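### The PHQ-ADS reliable change index from T1 to T3 cannot be computed on the printed schedule, because Table 2 collects the PHQ-ADS at screening only

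*Protocol article*

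**What the plan says.** Four places in the protocol article bear on this.

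- **Section 3.2.4.2, domain 5:** "Symptoms of anxiety and depression will be measured using the Patient Health Questionnaire Anxiety and Depression Scale". The scale has 16 items and a range of 0 to 48.
- **Section 3.2.4.2, domain 6:** the benefit-risk assessment includes reliable improvement and deterioration by the Jacobson-Truax index "for the PHQ-ADS, indicating a decrease or increase of >1.96 from T1 to T3". The same paragraph lists, among the measures taken at T2, "item 9 of the PHQ-ADS (73), and item 9 from the BDI-II (80".
- **Section 3.2.4.1 and Table 2:** the text sets the later time points as "baseline (T1), 10 days post-randomization (T2, only IG), and 4 weeks post-randomization (T3, post-intervention", with T0 as screening. Table 2 heads its columns "Screening T0 Baseline T1 10 Days T2 Post". Its PHQ-ADS row is "PHQ-ADS Anxiety and depression x", and that single mark stands in the screening column. Its PHQ-4 row is "PHQ-4 Anxiety and depression x x x x", with marks at baseline, post, daily and every four days.
- **Table 3, criterion 6:** "Pre-post change in the PHQ-4 scores compared to the control group (depression and anxiety subscales". This uses the PHQ-4, as does the sample-size paragraph in Section 3.2.3.

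Section 3.2.6 (Safety concept) places PHQ-ADS item 9 at screening.

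**The concern.** A change index is prespecified on a scale that the schedule does not collect at either end of the stated interval. If sites and the survey build follow Table 2, the PHQ-ADS is answered once, before enrolment, and never again.

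The part at stake is a stated safety analysis. Section 3.2.5.1 calls the intervention feasible only if every Table 3 criterion is yellow or green. Criterion 7 (risk-benefit ratio) lists symptom deterioration under red. Domain 6, which describes how the benefit-risk ratio is assessed, gives only the PHQ-ADS index as its rule for calling a symptom change reliable. A post-intervention PHQ-ADS that was not collected at 4 weeks cannot be recovered later, so the conflict has to be settled before participants reach that assessment.

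**Working it through.** No figure in the plan needs reproducing. The check is whether the schedule supplies what the stated analysis needs.

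**Step 1: what the index needs.** The Jacobson-Truax index is

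RCI = (post total − pre total) / (SD_pre × √(2 × (1 − r))).

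For r, the article gives a PHQ-ADS reliability of α = 0.88–0.92. The factor multiplying the SD is therefore √(2 × 0.12) = 0.490 down to √(2 × 0.08) = 0.400. An SD can be taken from the screening scores. The denominator can therefore be formed, and the question is the numerator, which needs two PHQ-ADS totals per participant.

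**Step 2: what is scheduled.** The rows of Table 2 at the points that matter are:

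| Scale | Screening | Baseline | 10 days | Post (4 weeks) |
|---|---|---|---|---|
| PHQ-ADS | yes | no | no | no |
| PHQ-4 | no | yes | no | yes |

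Each participant has one PHQ-ADS total. The numerator is undefined for all: 0 of 60 planned participants would have an RCI.

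**Step 3: whether another reading supplies the second score.**

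- *Text labels (T1 baseline, T3 4 weeks):* Table 2 has no PHQ-ADS at either point.
- *Screening score used as the pre value:* a post total is still missing.
- *Table 2's own labels (T1 is 10 days):* there is no PHQ-ADS at 10 days, and the table has no T3.
- *PHQ-ADS item 9 at T2, as in domain 6:* this is one item out of 16 and does not give the total. Section 3.2.6 puts that item at screening, in agreement with Table 2.

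**Step 4: the labels.** The text and the caption of Figure 1 use T0 screening, T1 baseline, T2 10 days and T3 4 weeks. Table 2 uses T0 baseline, T1 10 days and T2 post. Section 3.2.4.2 mixes the two systems. Its index runs to T3, which exists only in the text's system. Its INEP-On is placed at T2, and Table 2 marks the INEP-On only in the post column, so that T2 follows the table's system.

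**Step 5: what is untouched.** Criterion 6 and the sample-size outcome use the PHQ-4, which has both a baseline and a post score. Domain 5 also has the CBTSQ, the TYDQ and the interviews. Domain 6 also has the INEP-On, BDI-II item 9 and documented adverse events.

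**The case against.** The best case on the other side has three parts.

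**Table 2 may simply lack a mark.** Domain 6 lists PHQ-ADS item 9 at T2, which is the post-assessment under Table 2's labels, so the authors may intend a full PHQ-ADS at post. This is possible, but Section 3.2.6 sides with Table 2, and Section 3.2.4.1 presents Table 2 as the overview of every assessment and instrument. A faulty extraction is unlikely, because the row reads cleanly and neighbouring rows (BDI-II item 9, with screening and post) carry their marks in the right columns. What stands is that the documents contradict each other. It is not established that the data will be lost.

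**Symptom change can still be judged.** This stands and sets the scope. Criterion 6 already grades reliable change on the PHQ-4 against control. Criterion 7 names no scale, so its deterioration entry could be read from PHQ-4 data. A reader might infer that the symptom outcome as a whole, or two of the six feasibility domains, cannot be assessed. The documents do not support that, given the measures that remain.

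**Further inferences go too far.** A reader might conclude that the full-scale trial would get no PHQ-ADS SD; screening does provide one, and only change and post-intervention data are missing. A reader might expect the screening score to drift through regression to the mean, or PHQ-4 answers to shift through repeated in-app testing. The documents give no basis for the direction or size of either, and the contradiction does not depend on them. Finally, the 1.96 might be taken as raw scale points. Because the text cites the Jacobson-Truax index, index units are the natural reading.

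**Conclusion.** The point holds in a limited form. As printed, the PHQ-ADS reliable change analysis of domain 6 and any PHQ-ADS change score or post-score ANCOVA under domain 5 cannot be run: no participant out of 60 would have the two totals required. The effect is confined to those analyses and, through them, to the stated basis for judging deterioration under Table 3 criterion 7.

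The conclusion assumes that Table 2 is the schedule actually followed. If the text is right and Table 2 is wrong, the analysis is possible and the error lies in the table. In either case the article contradicts itself on a prespecified safety analysis, and the time-point labels do not settle which part is meant.

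**What to change.** Reconcile Section 3.2.4.2, Section 3.2.6 and Table 2 in one of two ways.

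- **(a) Keep the PHQ-ADS.** Mark the full 16-item scale in Table 2 at baseline and at the 4-week post-assessment, in both arms, and compute the index from those two totals. The cost is 16 more items at two online assessments. Because the scale includes item 9 on suicidal thoughts, Section 3.2.6 should say that the existing safety procedure covers the item at these points.
- **(b) Move to the PHQ-4.** Restate domains 5 and 6 so that symptom change and the reliable change index use the PHQ-4, already collected at baseline and post. This adds no burden for participants. The text should then say whether the index applies to the total or to the subscales named in criterion 6, and which reliability coefficient is used, since the article gives one for the PHQ-ADS but none for the PHQ-4.

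Under either option, use one set of time-point labels throughout the text, Figure 1 and Table 2, and correct the T2 references in Sections 3.2.4.2, 3.2.4.3 and 3.2.6 to match. This is an editorial change only.
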